#### Fitness test

The fitness test includes all components of health-related fitness by measuring blood pressure, heart rate, height, weight, percentage fat, waist circumference, flexibility of the hamstring, shoulders and back, arm and leg strength and endurance, dynamic balance, blood glucose, cholesterol, and cardio-respiratory endurance. To ensure that it is safe for them to participate in the fitness test, potential participants must first pass the Par-q questionnaire.

#### Questionnaire

The questionnaire will retrieve information about physical activity behavior, sedentary behavior, stages of changes, experienced health, self-management, motivation, self- efficacy, experienced health gains, knowledge, goals, and healthcare use.

#### Sample size calculation

The study population of the one-group pretest/ post-test will consists of adults who start a lifestyle program arranged by, or with the help of, the CSC in one of the nine municipalities. Inclusion will be determined by convenience sampling. The sample size calculation is based on alpha = 0.05 and power = 0.80 and assumes additionally:The primary outcome measure is maintenance of physical activity behavior after a lifestyle program, by participating in a local sports or exercise activity. Pilot data from the BeweegKuur revealed that 10–30 %, depending on the context, of the participants continue participating in local sports facilities after the lifestyle program [[name], Personal Communication, November 2012]. The expected value for this study is 40 % because of the introduction of the CSC, although 20 % is set as the criterion for this sample size calculation.Some of the effects will be explainable by differences in support, lifestyle programs, and context in each neighborhood. There are no data available from the BeweegKuur about the intra-class correlation coefficient (ICC). An ICC of 0.15 is assumed, based on research into common values and similar interventions [62–65].

The required number of participants is 414, which will lead to 258 independent observations due to a design effect of 1.6. On the assumption of a drop-out rate of 10 % during the lifestyle program [66], 10 % at T1, and 20 % at T2 [67], a baseline sample of 640 participants is required.

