### Study population

Nine municipalities, spread over the Netherlands, were selected through convenience sampling based on project partners’ contacts. Inclusion criteria were: 1) the municipality has appointed a CSC for the next four years (until 2017) with the task of connecting primary care, sport, and physical activity and 2) the CSC’s target group is comprised of adults. The particular CSC was selected in consultation with the representative civil servant in each municipality; the total number of CSCs in the study is 14. This is approximately 15 % of the CSCs employed to connect primary care and sport for adults in the Netherlands [45].

Each research question has additional participants such as professionals in the alliances of CSCs, national policymakers, and experts in the field of health, sports, and physical activity policy, residents, primary care professionals, sports professionals, and participants in lifestyle interventions. These are explained in the description of each research question; an overview is shown in Table 1.

**Table 1 Tab1:** Study overview – frameworks, methods, tools, participants, and repeats

Research question	Framework	Method	Tools	Participants	Repeats
SI.1		Literature review			1
	HALL framework	Interviews	Network Analysis Tool	14 CSCs^1^	6
			Timeline Method		
			Levels of Collaborations Survey		
		Focus groups	Coordinated Action Checklist	14 CSCs^1^ and professionals in their alliances	3
			Timeline Method		
SI.2	ADEPT model	Document analysis	Checklist based on ADEPT model		4
		Interviews	Local public health capacity mapping checklist	9 policymakers of the selected municipalities	1
SI.3		Focus groups	Effect arena	14 CSCs^1^, their alliances and residents	2
SII.1		Interviews		14 CSCs^1^	6
SII.2		Literature study			1
		Delphi study		Representative sample of the following professions; general practitioner, practitioner nurse, physiotherapist, coordinator social neighborhood team, public health policy coordinator, trainers, chairmen of sports clubs, CSCs^1^ and lifestyle programs participants	3–4
SII.3	Toronto Model	Fitness tests		Adults who participate in lifestyle programs arranged by, or with the help of, the CSC^1^	3
	Conceptual framework	Questionnaires			

^1^Care Sport Connectors

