### Data analysis Study II

The first round of the Delphi study will be analyzed via content analysis. Similar answers will be combined into themes with the use of Atlas.ti 7.0, and each theme will be used to generate statements. The statements, scored on a 7-point Likert scale, in the subsequent rounds will be analyzed with the help of the SPSS program. Measures of central tendency and level of dispersion will be used. Agreement is reached if 80 % of respondents’ responses fall within two categories on a 7-point Likert scale.

The quantitative data gathered via the fitness tests and questionnaires will be analyzed using the SPSS program. Multivariate techniques make it possible to test whether there is a relation between dependent variables such as physical activity behavior or motivation and independent variables such as gender, age, and nationality. Longitudinal data analysis will be used to study the individual development of the outcome variables and to determine whether there is a relationship with the individual development of other variables.

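### A design effect of 1.6 with an ICC of 0.15 needs about 83 independent clusters of five, which the article never states, so 258 independent observations are unsupported

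*Protocol article*

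**What the plan says.** Under the heading Sample size calculation in Study II, the protocol article fixes the error rates ("The sample size calculation is based on alpha = 0.05 and power = 0.80"). The primary outcome is continued participation in a local sport or exercise activity after the lifestyle programme. Pilot data from an earlier Dutch lifestyle programme are reported as 10–30% continuing, varying with context. The authors anticipate 40% here, which they ascribe to the new CSC role, "although 20 % is set as the criterion for this sample size calculation".

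Clustering is introduced with the sentence "Some of the effects will be explainable by differences in support, lifestyle programs, and context in each neighborhood", and then "An ICC of 0.15 is assumed, based on research into common values and similar interventions". The section concludes that 414 participants are required, "which will lead to 258 independent observations due to a design effect of 1.6", and that dropout of 10%, 10% and 20% raises the baseline sample to 640.

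It gives no cluster unit, cluster size or number of clusters. The Study population section says there are nine municipalities and that "the total number of CSCs in the study is 14". The article gives no number of neighbourhoods or lifestyle programmes.

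**The concern.** A design effect follows from an ICC and a cluster size. The article gives the ICC and the result but not the size, and the implied size is far below what its counted units would produce. Participants come through 14 CSCs in nine municipalities, which means about 30 or 46 analysed people per unit rather than five.

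The design effect turns 414 people into 258 independent observations, so it carries the primary outcome's sample size and, through the dropout allowance, the 640 baseline target. If it is too small, the trial holds less information on maintenance than it reports, and a reader has no means of checking by how much.

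**Working it through.** **Inputs.** From Sample size calculation: ICC 0.15, design effect (DE) 1.6, 414 analysed, 258 independent observations, dropout 10%/10%/20%, baseline 640, criterion 20%, expected 40%, pilot range 10–30%. From Study population: 14 CSCs, nine municipalities.

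**1. The article's own figures.** Effective n = N/DE = 414/1.6 = 258.75, which matches 258. Baseline = 414/(0.9 × 0.9 × 0.8) = 638.9, which matches 640. The divisions are right; the question is the 1.6.

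**2. What 1.6 implies.** For equal clusters of size m, DE = 1 + (m − 1) × ICC. Then m = 1 + 0.6/0.15 = 5, and 414/5 = 82.8, or about 83 clusters. That is 82.8/14 = 5.9 clusters per CSC.

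**3. The units the article counts, at ICC 0.15.** The ceiling is the limit of effective n as enrolment grows without bound, which is k/ICC for k clusters.

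| Cluster unit | m | DE | Effective n | Ceiling k/ICC |
|---|---|---|---|---|
| 14 CSCs | 414/14 = 29.57 | 1 + 28.57 × 0.15 = 5.29 | 414/5.29 = 78 | 14/0.15 = 93 |
| 9 municipalities | 414/9 = 46 | 1 + 45 × 0.15 = 7.75 | 414/7.75 = 53 | 9/0.15 = 60 |

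Keeping 1.6 at these levels would need an ICC of 0.6/28.57 = 0.021 or 0.6/45 = 0.013 in place of 0.15.

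**4. Programmes as clusters, independent of one another (sizes assumed).** With m = 5, effective n is 259. With m = 10, DE is 2.35 and effective n 176. With m = 15, DE is 3.10 and effective n 134.

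**5. Programmes of five nested in 14 CSCs.** Let ρ be the correlation between people in different programmes of the same CSC. Then DE = 1 + (5 − 1) × 0.15 + (29.57 − 5) × ρ. The article gives no ρ. As an assumption, take the pilot range of 10–30% as the spread between contexts, with mean 20% and total variance 0.2 × 0.8 = 0.16.
- Contexts spread evenly over the range: variance 0.2²/12 = 0.0033, ρ = 0.021, DE = 1.6 + 24.57 × 0.021 = 2.1, effective n about 196.
- Contexts split between the two extremes: variance 0.1² = 0.01, ρ = 0.0625, DE = 1.6 + 24.57 × 0.0625 = 3.1, effective n about 132.

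**6. Precision, which needs no alternative.** The 95% half-width around 20% is 1.96 × √(0.16/n): 4.9 points at 258, 5.6 at 196, 6.8 at 132, 8.9 at 78 and 10.7 at 53.

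**7. The alternative behind 258.** It could not be recovered. A one-sample test of 20% against 40% needs 29–36 observations (one- or two-sided), and a two-group comparison of those values needs 128–164 in total. A one-sample test of 20% against 30% needs 109–137. None gives 258.

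**The case against.** The strongest reply is that the article never makes the CSC or the municipality the cluster. It names lifestyle programmes and neighbourhoods among the sources of clustering, and m comes out at exactly five, which looks deliberate. Five analysed people correspond to 5 × 640/414, or about eight starters per programme. About six programmes per CSC over three years is not absurd, and nothing in the article contradicts it. This stands: a reader might infer from step 3 that 414 people can never supply 258 independent observations, but that follows only if an ICC of 0.15 acts at CSC or municipality level, which the article does not say.

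The programme reading does not secure 1.6, however. The article attributes the clustering also to support and to neighbourhood context, which programmes under one CSC may share, and it reports pilot maintenance that varied with context. A design effect built from independent groups of five sets that shared correlation to zero.

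A second tempting inference is that the 80% power is lost. If 258 were exactly the 80% requirement, the same effect would have two-sided power of about 34% at an effective 78 and 25% at 53. But the alternative is unstated. For the one pair of criterion and expected values the article gives, 20% and 40%, a one-sample test keeps about 98% or 92% power (normal approximation; so few clusters would lower this somewhat). Loss of power is therefore not shown.

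Third, the short wording of Data analysis Study II ("Longitudinal data analysis will be used to study the individual development of the outcome variables") does not exclude multilevel models, and their specification may sit in a fuller document. It is not evidence that clustering will be ignored.

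Finally, the article itself says that, without a control case, a general effect of CSCs cannot be estimated. That limits the consequences but does not repair the calculation.

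**Conclusion.** The point holds in conditional form. The stated ICC and design effect fit together only under about 83 independent clusters of five analysed participants, a structure the article does not state. At CSC or municipality level, 1.6 is incompatible with an ICC of 0.15: effective n is about 78 or 53, and 258 lies above the ceilings of 93 and 60. With programmes of five as clusters, allowing for shared CSC support and context brings effective n to about 130–200. That range rests on equal cluster sizes and on reading the pilot's 10–30% as between-context spread across 14 CSCs.

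The 258 independent observations and the 0.80 power attached to them are thus unsupported and probably too favourable. The size of any power loss cannot be determined from the article.

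**What to change.** In Sample size calculation:
- name the cluster unit and give its expected number and analysed size;
- recompute the design effect for that unit, including a stated correlation between participants of the same CSC, with a range if it is uncertain;
- replace the 258 and the 0.80 power with the resulting effective sample size, and with power or confidence-interval width for a stated alternative and test.

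If programmes of about five completers are intended, say so, give the roughly 83 programmes this requires, and add the CSC-level term. Account for the same clustering in the primary analysis of maintenance.

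The cost is rewording and a short recalculation. No extra participants are needed; the price is a less favourable stated figure.

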### Data analysis Study II

The first round of the Delphi study will be analyzed via content analysis. Similar answers will be combined into themes with the use of Atlas.ti 7.0, and each theme will be used to generate statements. The statements, scored on a 7-point Likert scale, in the subsequent rounds will be analyzed with the help of the SPSS program. Measures of central tendency and level of dispersion will be used. Agreement is reached if 80 % of respondents’ responses fall within two categories on a 7-point Likert scale.

The quantitative data gathered via the fitness tests and questionnaires will be analyzed using the SPSS program. Multivariate techniques make it possible to test whether there is a relation between dependent variables such as physical activity behavior or motivation and independent variables such as gender, age, and nationality. Longitudinal data analysis will be used to study the individual development of the outcome variables and to determine whether there is a relationship with the individual development of other variables.

## Discussion

This study is designed to provide information about the implementation of the CSC function in nine municipalities, spread over the Netherlands. Through a mixed methods design, it will be possible to examine whether CSCs can achieve their objectives: 1) to connect primary care, sport and physical activity and 2) to increase the number of physically active residents. Besides this, the study will reveal whether a broker role contributes to improved intersectoral collaboration, increased participation by residents, transferal of patients from primary care to physical activity facilities, and self-management. Facilitators and barriers that are brought to light will be transformed into practical tools for CSCs and recommendations for supportive organizations to advance health promotion theory and practice in the Netherlands.

### Relevance

The number of people with one or more chronic diseases is increasing, and this trend could be reduced by promoting physical activity. A healthier population will benefit society at large through, for example, enhanced wellbeing, a decrease in healthcare costs, and higher work productivity [68]. The CSC function is implemented under national and local policy in order to reverse this trend, and this study will reveal whether CSCs are able to fulfill these policy aspiration.

The novelty of the CSC function means that there is no clear job description with required competencies. Therefore, it is not yet clear for what CSCs can and should be held accountable. By the use of qualitative and quantitative methods in multiple cases, it is possible to get insight into results achieved, opportunities, and realistic expectations. In addition, this study will generate actionable knowledge with stakeholders to improve practice immediately. Process evaluation makes it possible to get insight into developments achieved because of the implementation of this actionable knowledge. Accurate actionable knowledge is very helpful for a new, developing function, especially because of the expanding number of Neighborhood Sport Coaches in the Netherlands. At the start of this study in 2012, 3.2 % of the 1850 FTE for Neighborhood Sport Coaches were employed as CSCs for adults in the Netherlands [69]. An in-depth study over 18 municipalities revealed that, in 2014, 12 % of the surveyed Neighborhood Sport Coaches focused on connecting primary care and sport [70].

### Strengths and limitations

The study design is optimized for internal and external validity because action research, process evaluation, and the one-group pretest/post design are combined. The principle of triangulation is continuously applied to optimize the reliability of this study, using multiple methods, multiple sources, and multiple cases [71, 72]. Internal validity is enhanced by triangulation of methods and resources, whereby results will be checked with other stakeholders. In addition, other verification techniques will be used, such as expert consultation and loop learning [43, 73]. External validity is enhanced by studying multiple cases. Case studies take place in real-life settings and provide insight into the why and how in practice. Similar results in different cases will make it possible to draw general conclusions. This will result in formulated preconditions and prerequisites for CSCs rather than the general effect of CSCs. Because of differences in contexts in the multiple cases and the absence of a control case without a CSC, the latter is not possible.

In this study, a one-group pretest /post design will be used to measure physical activity maintenance and health gains. This design is appropriate to follow patients and residents who participate in activities and interventions, organized by, or with the help of, the 14 CSCs in this study, over an extended period. Individual-level results obtained from the one-group pretest/post design will be linked with results at the intervention, the environment and the policy level in order to be able to explain why changes in physical activity behavior and health have taken place, or not. For this study, a randomized controlled trial design is not appropriate, because it is impossible to arrange suitable control groups in real-life settings that resemble the contexts of the cases in our study. The context is different in each case and is exposed to continual change over time because of the action of the CSC, but probably also because of other stakeholders and events outside the control of the study [74]. Linking and integrating results gained by multiple methods at different levels will result in a validated assessment of the impact of CSCs on connecting the primary care and sports sectors, changes in residents’ physical activity behavior will be ascertained and the circumstances in which this will happen will be established [75]. The assessment, in combination with general lessons learned from the different case studies, will make it possible to determine whether CSCs are able to fulfill the policy aspiration and whether it would be beneficial to extend this function over more municipalities.

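### The article says a general effect of the Care Sport Connector cannot be obtained without a control case, yet promises to determine whether the policy aspiration is met and whether extension would be beneficial

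*Protocol article*

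**What the plan says.** **The limit.** Strengths and limitations describes what the study will produce: "This will result in formulated preconditions and prerequisites for CSCs rather than the general effect of CSCs". The reason follows: "Because of differences in contexts in the multiple cases and the absence of a control case without a CSC, the latter is not possible". The next paragraph adds that each context keeps changing, partly through the CSC but probably also through other stakeholders and outside events.

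**The promise.** That same paragraph ends by saying that the assessment, together with lessons from the cases, will "make it possible to determine whether CSCs are able to fulfill the policy aspiration and whether it would be beneficial to extend this function", there with reference to further municipalities. The Discussion part of the abstract makes the same statement without the limitation. Relevance says that "this study will reveal whether CSCs are able to fulfill these policy aspiration".

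**The softer statement.** The opening paragraph of the Discussion says "it will be possible to examine whether CSCs can achieve their objectives", the second of these being "2) to increase the number of physically active residents". It goes on to say that the study will reveal whether a broker role contributes to, among other things, greater participation by residents.

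**The data.** The nine municipalities were "selected through convenience sampling" through project partners' contacts. SII.3 uses a one-group pretest/post-test design with measurements at programme start, at programme end and one year after the start. The Sample size calculation section limits its population to adults starting a programme arranged by or with the help of a CSC, again included by convenience sampling.

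**The concern.** Whether the policy aspiration is met, and whether the CSC function deserves extension, are questions about what the CSC brings about compared with its absence. The article rules out exactly that comparison and then announces an answer. If the final report follows the text as written, its main policy conclusion will contradict the study's own limitation, and a decision on extending a publicly funded function could rest on it. There is a second gap. The aspiration concerns how many residents are active, whereas the individual outcomes are measured in people who have already entered a programme.

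**Working it through.** No arithmetic decides this point; it is settled by setting the statements side by side.

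1. **What the aspiration is.** The Background defines the intended outcome of the CSC role as more residents participating in local sports facilities and being active in their own neighbourhood. That is an increase at resident level, expected to follow from the CSC.
2. **What a verdict on it needs.** To say that CSCs achieve this, or that more municipalities would gain from them, one needs (a) a measure of resident activity and (b) a way to separate the CSC from whatever else changed.
3. **Is (b) available?** No, by the article's own account: "the absence of a control case without a CSC, the latter is not possible". It also acknowledges concurrent outside influences.
4. **Is (a) available?** Not at population level in what the article describes. Table 1 lists fitness tests and questionnaires for programme participants. Residents otherwise appear in the SI.3 focus groups at the end of the project, which collect perceived impact and benefits.
5. **Which CSCs are observed?** The Study design section says that action research feeds results back to CSCs and stakeholders so that they can adjust their practice. The observed CSCs are therefore CSCs working with that support.

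**Does sample size help?** The article gives 414 participants and a design effect of 1.6: 414 / 1.6 = 258.75, against a stated 258 independent observations. Take 258 as given. If 40% of participants continue in a local activity, the 95% interval is 0.40 ± 1.96 × √(0.40 × 0.60 / 258), or about 34.0% to 46.0%. That is precision about the continuation rate in CSC programmes only.

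The one external benchmark is the BeweegKuur pilot range of 10–30%, which the article calls context-dependent. As an illustration, assume that the 20% criterion is the reference value and that favourable context alone yields 30%, the top of that range. The interval is 0.30 ± 1.96 × √(0.30 × 0.70 / 258), or about 24.4% to 35.6%. It lies wholly above 20% although, by assumption, the CSC contributed nothing. More participants would narrow the interval around the same unattributable figure.

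**The case against.** The best defence is that the limitation is stated openly, directly before the disputed paragraph; that case studies legitimately inform policy on processes, alliances and preconditions; and that the authors explain why suitable control groups could not be arranged. All of this is fair, and the point asks for no randomised trial. But disclosing a limit does not license the opposite conclusion a paragraph later, and the abstract carries the conclusion without the limit.

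Several stronger readings are tempting and are not supported:

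- A reader might infer that the validated assessment promised in the abstract and in Strengths and limitations covers effects on residents. Its stated object is the connection between the primary care and sports sectors, which is the subject of Study I. For residents, Strengths and limitations speaks of ascertaining changes and their circumstances.
- A reader might infer that the opening of the Discussion also gives a verdict on extension. It does not, and its verb on the objectives is the softer one in "it will be possible to examine whether CSCs can achieve their objectives". Those objectives belong to the CSCs and derive from policy, so the investigators need not rewrite them.
- A reader might infer that all quantitative data come from programme joiners, or that no resident is measured. Study I compares collaboration scores over time and gives policymakers a questionnaire, and the Delphi study scores statements. Programme participants are themselves adults from the neighbourhood. What is absent from the description is a population-level count.
- A reader might infer that the SII.1 programme table omits participant numbers. Its columns are not shown, so this cannot be known.
- A reader might set the 20-point width of the pilot range against the 20-point gap between criterion and expected value as a measure of bias. The match is coincidental and measures nothing.

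**Conclusion.** The contradiction stands. The article excludes a general CSC effect and then, in the abstract and in Strengths and limitations, claims to determine two things that require one; Relevance repeats the first of them. The statement in the Discussion that the broker role's contribution to resident participation will be revealed goes too far for the same reason. The design can show change and maintenance in a convenience sample of programme starters. It can also describe the processes and preconditions that accompanied them, in CSCs that received action-research feedback. It cannot show that the number of active residents rose, or that extension is beneficial.

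The point has no numerical size: it changes what may be concluded, not the sample, the measurements or the analysis. It rests on the article's own description of its design and on reading the policy aspiration as the Background defines it. It is worth correcting because the affected sentences are the ones a policy reader will use.

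**What to change.** In the abstract's Discussion, in Relevance, and in the second paragraph of Strengths and limitations, replace the claims about the policy aspiration and about extension. The replacement should say that the study will describe change and maintenance observed among participants of CSC-arranged programmes, without attributing it to the CSC, together with the processes and preconditions associated with it, for CSCs that received action-research feedback. In the opening paragraph of the Discussion, reword the clause on the broker role contributing to residents' participation in the same way; the CSCs' own objectives can stay as they are. Add one sentence saying that this design cannot determine whether the number of active residents increases or whether extending the function is beneficial.

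The cost is a few edited sentences and a weaker stated conclusion. No data collection, sample size or analysis changes.
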